## Abstract

Supplemental Digital Content is available in the text

## Introduction

1

FC is one of the common functional gastrointestinal disorders that affects a large population around the globe. Prevalence rate of FC varies greatly from 1.9% to 27.2% in North America population with the highest estimates from 12% to 19%;^[1]^ In China, it varies from 6% to 13% for the period of 2010 to 2016.^[2,3]^ Gender, age, diet, education, and neurological diseases are the main influencing factors for FC.^[4,5]^ FC is protracted and prone to recurrence, thus affects patient's quality of life adversely along with increase in overall medical costs.^[6]^

Prolonged colonic transit time (slow transit constipation, STC), pelvic floor muscles dysfunction (functional defecation disorder) and their combined effects are the well-established mechanisms involved in the development of FC. The latest diagnosis of FC is based on the criteria of Rome IV Standard, including laborious defecation, dry or lumpy stool, incomplete defecation, anorectal obstruction, prolonged defecation cycle, and manually assisted defecation. Two or more of the above items need to be included with at least 25% frequency for each one. Meanwhile, loose stool is rarely present without laxative and irritable bowel syndrome (IBS) should be excluded.^[7]^ Dry or lumpy stool is not necessary for FC diagnosis as many patients whose stool is not that dry or lumpy but sticky, complain of difficult defecation. However, there are few studies on this kind of constipation. In TCM, gastrointestinal damp-heat syndrome is the major FC syndrome that accounts for almost 32.5% FC cases.^[8]^ Heat evil results in formation of dry or lumpy stool, which is in agreement with typical understanding of FC in western medicine, while damp evil inclines to cause sticky stool in TCM theory. Based on that, the classification therapy shows greater therapeutic efficacy against FC with gastrointestinal damp-heat syndrome. Thus, we can divide this FC syndrome into 2 subtypes that are heat more than damp syndrome (typical functional constipation, TFC) and damp more than heat syndrome (atypical functional constipation, aTFC). Drugs therapy is still the main method for effective FC treatment. For TFC, Macrogol 4000 Powder is one of the effective and safe drugs, which can increase the average number of defecation per week by 1.9 times as compared to placebo.^[9]^ On other hand, the effectiveness of Chinese herb for aTFC could reach 66.7% to 72.7%.^[10]^ However, it has been recently reported that only 25.1% among 6318 Chinese adults with constipation selected laxatives, while 81.7% of them preferred lifestyle and dietary changes as treatment option.^[11]^ The results of a current study have shown a close relationship between the intestinal flora and FC,^[12]^ but their causal relationship still remains unclear.^[13]^ Different eating habits such as low intake of water, fruits and vegetables and high intake of spicy, greasy food all contribute to the increased prevalence of FC.^[14]^ Similarly, increased intake of whole fruits, especially fruit fiber can protect colonic gastrointestinal health.^[15]^ Additionally, another report indicated that five days of dietary changes could quickly alter the human intestinal flora.^[16]^ Therefore, the correlation between diet and constipation may be explained by changing the intestinal flora.

LVD is a set of dietary programs summarized in many years of clinical experience. The light diet means low fat, low stimulation and not prominent in cold, hot, sour, bitter, sweet, spicy, and salty; The vegetarian diet means meat, eggs and milk should be avoided and vegetables or fresh fruits should be ingested as much as possible. Several studies have proved the above mentioned food to be related with constipation.^[14]^ The diet can maintain the therapeutic effects in both subtypes of constipation after drug withdrawal, thus long-term diet intervention is realizable.^[17,18]^ To date, there is no rigorous evidence to support the effectiveness and safety of LVD, thus this needs authentication based on clinical trials in human subjects. In this protocol, we will design a randomized controlled trial (RCT) to systematically verify that point.

## Methods and design

2

### Study objective and hypotheses

2.1

This exploratory study aims to investigate the therapeutic effects of LVD and its supplementary effects to drugs on FC with gastrointestinal damp-heat syndrome.

### Study design

2.2

The protocol was drafted using the SPIRIT guidelines and the results will be reported following the checklist of the Consolidated Standards of Reporting Trials (CONSORT) statement (see Supplementary Table 1). All the participants will be informed about the study purpose and their signed informed consent will be obtained before joining this parallel-group study. A total of 92 participants will be recruited in each TFC or aTFC subtype following the inclusion and exclusion criteria. Then they will be allocated to drug + diet group, placebo + diet group, drug group and placebo group randomly at 1:1:1:1 ratio. The positive drugs are Macrogol 4000 Powder (Forlax, Beaufort Ipsen Industrie) and Chinese herb powder for TFC and aTFC groups respectively. Outcomes will be evaluated at baseline, the 14th day (followed-up by telephone) and 28th day by researchers blinded to the groups. Participants will be informed whether diet intervention is acted by the enrollment number and obtain the “drug” corresponding to the number, but they and the researchers will not know whether they are receiving a drug or a placebo. The whole study design is illustrated (see Fig. 1). A SPIRIT figure for the schedule of enrolment, interventions and assessments is also presented (see Fig. 2).

**Figure 1 F1:**
[figure not shown]
Study design. CSBM/W = complete spontaneous bowel movements per week, CSS = constipation-related symptom rating scale, TCMSS = traditional Chinese medicine syndrome scale, 48-h GITT = 48-hour gastrointestinal transit time, HRAM = high resolution anorectal manometry, FFD = fecal flora detection, BR = blood routine, LKF = liver and kidney function, AEs = adverse events, DQ = diet quality, DCR = dietary compliance rate.

**Figure 2 F2:**
[figure not shown]
SPIRIT figure: schedule of enrolment, interventions and assessments. CSBM/W = complete spontaneous bowel movements per week, CSS = constipation-related symptom rating scale, TCMSS = traditional Chinese medicine syndrome scale, 48-hour GITT = 48-hour gastrointestinal transit time, HRAM = high resolution anorectal manometry, FFD = fecal flora detection, BR = blood routine, LKF = liver and kidney function, AEs = adverse events, DQ = diet quality, DCR = dietary compliance rate.

### Exploratory study

2.3

LVD is original and RCT on LVD has not been investigated so far, thus it is highly innovative. Furthermore, studies on 2 subtypes of the major syndrome of FC can supplement the deficiency in traditional understanding of FC.

### Diagnostic criteria of FC with damp-heat syndrome

2.4

Diagnosis of FC with damp-heat syndrome must satisfy both Rome IV criteria of FC and TCM criteria of gastrointestinal damp-heat syndrome (see Supplementary Table 2),^[7]^ referring to the relevant syndrome provisions of the Guiding Principles of Clinical Research on New Drugs of TCM.^[19]^

### Inclusion criteria, exclusion criteria, and exit criteria

2.5

Participants must meet inclusion criteria (see Table 1) and be excluded from exclusion criteria (see Table 1), while exit criteria (see Table 1) are set for participants who cannot complete the study. Once a patient is included in the trial, the researchers in our team will keep in touch with him/ her and try to solve the problems during the treatment to reduce the loss of the intervention. During the trial, patients have the right to withdraw at any condition and will not affect subsequent treatment. The data will be recorded truthfully for further analysis.

**Table 1 T1:**
[figure not shown]
The inclusion criteria, exclusion criteria, and exit criteria for the trial.

### Sample size

2.6

Due to the lack of relevant evidence, this is an exploratory study with small sample size. A total of 92 participants for each subtype will be recruited and will be further divided in four sub-groups (23 participants in every sub-group).

### Recruitment

2.7

Participants will be recruited from the outpatients and inpatients of Gastroenterology Department and TCM Gastroenterology Department in China-Japan Friendship Hospital in Beijing through roll-up banners, posters, Wechat and the hospital official website. Two or more experts (at least 1 from Gastroenterology Department and 1 from TCM Gastroenterology Department) will decide the eligibility unanimously following the inclusion and exclusion criteria. It will be insured that both physicians and patients have no financial interests. All eligible recruiters will sign a written informed consent and those who accept the purpose, benefits and adverse effects of the study, will be enrolled.

### Interventions

2.8

After the patients are enrolled, they will finish a questionnaire (baseline information) and the relevant examinations (48-h GITT, HRAM, FFD, BR, LKF). Previous studies have reported Forlax and Chinese herb as effective drugs for the treatment of TFC^[9]^ and aTFC^[20]^ respectively. So, the drug used for the treatment of TFC subtype is Forlax. The placebo will be a kind of white powder made from orange essence, saccharin sodium and dextrin (Shanghai Aipu Food Industry Corporation) according to 0.2:0.015:100 (w/w) and is similar to Forlax in shape and color. Both Forlax and placebo will be vacuum packaged as 10 g per pack using same type of aluminum foil. The drug in aTFC subtype will be Chinese herb powder dried by Chinese herb decoction (Tongrentang Chinese Medicine) from clinical prescription (see Table 2), and the placebo will be a kind of brown powder made from caramel pigment and dextrin (Shanghai Aipu Food Industry Corporation) at 0.4:10 (w/w). Both the Chinese herb powder and placebo will be vacuum packaged as 15 g per pack using same type of aluminum foil. The drugs and placebos will be taken twice a day, one pack at a time, flushed with warm boiled water, half an hour after breakfast and dinner. The contents of LVD are as following:

(1)Taboo spicy (especially chili, pepper), irritating food, wine, fried food, grilled food, dry nuts, mutton, leek, toonasinensis and so on.(2)Avoid meat, eggs, milk, drinking coffee and strong tea.(3)The staple food are cereals and grains, take vegetables and fruits as much as possible.(4)Eat medicinal gruel: millet (main ingredients), coix seed, red bean that are mixed and cooked and eaten 1 to 2 times a day.(5)More than half of the staple food is potato (such as sweet potato and potato).(6)Diet must accord with three meals a day, regular quantitative with abstinence from drinking

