### Randomization, allocation concealment and partly double-blind

2.9

Two groups, each one of 92 independent random numbers, will be generated using Excel 2013 software (Microsoft Corporation, Redmond, Washington) by the third party that does not participate in the study, and will be divided by 4. The remainder will be 1 for group A, 2 for group B, 3 for group C and 0 for group D. A, B, C, D are prescribed as diet + drug, diet + placebo, drug and placebo group, respectively. The number of the drug will be reserved and will be encapsulated and stored in opaque envelopes, preserved by the third party. When a patient is enrolled, an envelope with a sequence number on its surface will be passed to the researchers. The researchers and patients will know whether diet is interfered and the drug number only, but not the corresponding drug or placebo group. When the trial is finished, the third party will uncover the blindness. It is difficult to conduct blinding since the diet intervention is a set of dietary principles, rather than specific food, so only drugs are double-blind to reduce the information bias.

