#### Primary outcome

2.12.2

The number of CSBM per week is the primary outcome. It is effective when the number before the intervention subtracted from the number after the intervention is more or equal to 1.

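### The placebo for the Chinese herb powder has no declared taste or smell match, so unblinding is a credible, unquantified risk to the patient-reported herb-versus-placebo comparisons in the aTFC subtype

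*Protocol article*

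**What the plan says.** Section 2.8 (Interventions) describes the two placebos differently.

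- **TFC (comparator Forlax, 10 g packs).** "The placebo will be a kind of white powder made from orange essence, saccharin sodium and dextrin", at 0.2:0.015:100 by weight. The article adds that it "is similar to Forlax in shape and color".
- **aTFC (comparator herb powder, 15 g packs).** "The drug in aTFC subtype will be Chinese herb powder dried by Chinese herb decoction", while "the placebo will be a kind of brown powder made from caramel pigment and dextrin", at 0.4:10 by weight. On matching, the text gives the brown colour and this: "Both the Chinese herb powder and placebo will be vacuum packaged as 15 g per pack using same type of aluminum foil". It makes no statement that the placebo resembles the herb powder.

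All four products are taken one pack at a time, twice a day, "flushed with warm boiled water", for 28 days.

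Section 2.9 explains that the diet intervention cannot readily be masked, "so only drugs are double-blind to reduce the information bias". Section 2.12.2 states: "The number of CSBM per week is the primary outcome". Section 2.8 has patients keep a defecation diary. In 2.12.3 the CSS uses a visual analogue scale of discomfort, and the TCMSS grades symptoms by their impact on the patient's life.

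**The concern.** Section 2.9 relies on the drug blind to limit information bias, and a drug blind is only as good as the match between the products. For aTFC, 2.8 gives a complete recipe for the placebo, and that recipe has a colourant and a bulking powder but no ingredient declared as a flavour or aroma. The comparator is a dried decoction of herbs. Both are loose powders taken with water, so no capsule or coating hides taste or smell.

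This is a property of the formula the article fixes. It is not a detail that a condensed article has left to a fuller document.

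If some aTFC patients recognise what they are taking, expectation can move diary counts, discomfort ratings and symptom grades. The apparent herb effect over placebo would then be partly an effect of knowing the allocation. The 48-h GITT, HRAM and fecal flora results are instrumental or laboratory measures and less open to this.

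**Working it through.** The plan states no figure for blinding quality, so there is none to reproduce. The check has three parts: what is in the packs, how often patients meet them, and which comparisons depend on the match.

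**1. Contents of a placebo pack (ratios and pack weights from 2.8).**

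aTFC, 15 g, ratio 0.4:10, total 10.4 parts:
- caramel pigment: 15 × 0.4 / 10.4 = 0.58 g
- dextrin: 15 × 10 / 10.4 = 14.42 g
- sum: 0.58 + 14.42 = 15.00 g, so no weight is left for another ingredient.

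TFC, 10 g, ratio 0.2:0.015:100, total 100.215 parts:
- orange essence: 10 × 0.2 / 100.215 = 0.020 g
- saccharin sodium: 10 × 0.015 / 100.215 = 0.0015 g
- the rest is dextrin.

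So one placebo has a declared flavouring and sweetener, and the other has neither.

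**2. Exposure.** Two packs a day × 28 days = 56 packs per patient. By the planned numbers in 2.6 (23 per arm), 2 × 23 = 46 aTFC patients receive the herb placebo and 46 the herb powder.

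**3. Which contrasts depend on the match (arms from 2.9).** A is diet + drug, B is diet + placebo, C is drug, D is placebo.

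| Contrast in aTFC | Powders compared | Depends on the placebo match? |
|---|---|---|
| A vs B | herb vs placebo, both on diet | Yes |
| C vs D | herb vs placebo, neither on diet | Yes |
| B vs D | placebo vs placebo | Not directly |
| A vs C | herb vs herb | Not directly |

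The objective in 2.1 concerns the diet's own effect and its supplementary effect to drugs. B vs D and A vs C isolate diet. In each, both arms take the same powder, and diet status is already known to the patient. The direct exposure is therefore limited to A vs B and C vs D, on the outcomes that rest on the patient's account.

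**The case against.** The strongest reply is that the document does not show that the blind would fail. It nowhere describes the taste or smell of the herb powder, and its component table (Table 2) is not available in the text at hand. That a dried decoction tastes of herbs, and that caramel pigment adds no useful flavour, are general expectations that the document does not state. The arms are parallel, so no patient compares the two powders. This stands: a reader might infer that the aTFC blind is likely to fail, and the document does not support that.

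Three further readings are tempting and also go too far.

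- *That drug masking is the only protection left.* Section 2.2 says outcomes are evaluated by researchers blinded to group. That sits awkwardly with 2.9, under which researchers know diet status, but it is a stated safeguard. Several secondary outcomes are also instrumental or laboratory measures.
- *That all aTFC results are compromised.* The diet contrasts use the same powder in both arms. One can argue that a group D patient who recognised the placebo would know they had neither drug nor diet, which could widen the expectation gap in B vs D. That is indirect and nothing in the document shows it.
- *That unequal blinding spoils a comparison between the subtypes.* Section 2.15 specifies no such comparison. The subtypes are randomised separately and receive different drugs.

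It can also be said that the TFC placebo is claimed to be similar only in shape and colour, so its taste match is not asserted either. That is correct. The difference is that its formula at least contains ingredients that provide taste and aroma.

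Finally, a matching statement or a blinding questionnaire may sit in a fuller document. Their absence from an article is not the point here. The point rests on the stated formula, which the objection leaves in place.

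**Conclusion.** The concern holds in limited form. As specified, the aTFC placebo is matched to the herb powder at most on colour, pack weight and foil, and its two ingredients leave no room for a flavour or aroma agent. With 56 loose-powder packs per patient, unblinding is a credible risk for the CSBM diary, CSS and TCMSS in A vs B and C vs D of the aTFC subtype.

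The size of any bias cannot be derived from the document, and failure of the blind is not demonstrated. The conclusion rests on two assumptions that the document does not settle: that the herb powder has a noticeable taste or smell, and that caramel pigment with dextrin does not reproduce it. If either is wrong, the risk shrinks accordingly. The change is worth making because it is cheap and because 2.9 relies on the drug blind.

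**What to change.** In 2.8, change the aTFC placebo formula to include a food-grade taste and smell match to the herb powder, and confirm the match by a simple tasting of the two products before release. The choice of ingredient should follow from the herb powder's actual taste and smell, which the article does not give. The placebo is already mixed from food ingredients, so the cost is a small reformulation and a short delay.

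Optionally, ask each patient at the existing day-28 follow-up whether they think they received drug or placebo, and report the answers by arm. This costs one question.

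If the blind is not shown to hold, the aTFC drug-versus-placebo results on patient-reported outcomes should be interpreted with that caveat. The diet contrasts do not need it on this ground.

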**Table 2 T2:**
[figure not shown]
The component of Chinese herb powder.

Patients with diet intervention should follow the above items and patients without diet intervention will continue their previous eating habits. The treatment period will last for 28 days. During the treatment period, patients will be required to keep a diary about diet and defecation. The diet diary will be designed with a semi-quantitative food frequency method, and the defecation diary will gather information about sensation, stool shape and duration of each defecation. On the 14th day, patients will be followed up via telephone to find out the situation during the treatment and count the average times of CSBM per week, the average scores of constipation symptoms and TCM syndrome in the first 14 days. After 28 days of treatment, a second follow-up will be carried out to understand situation of constipation (the same to the first follow-up) and to ask the patients to finish the examinations (48-hour GITT, HRAM, BR, LKF). Fecal flora of fresh stool (<30 minutes) from patients will also be reviewed and the diaries will be taken back. During the intervention, the patients will keep in touch with the researchers for queries about the treatment if any to control the exit rate and any other drugs that can relieve constipation are forbidden.

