### Emergency unblinding

2.10

In case of any serious adverse events (SAEs) or emergency, the researcher will report to the supervisor and the main researcher to decide whether to open the emergency letter. Once opened, the case will be treated as exfoliated, excluded from the efficacy analysis, but will remain included in the adverse reaction analysis. Details of the unblinding cause, date, treatment situation and results will be reported in the case report form (CRF) and will be signed by the administrator.

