#### Safety outcomes

2.12.4

Safety parameters include AEs and laboratory examinations (BR, LKF).

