### Planned statistical analysis

2.15

Continuous variables will be described as the mean ± standard deviation (SD), median or interquartile range (IQR). The number of cases, frequency, the rate and the constituent ratio will be described by categorical variables. Variance analysis will be used for continuous variables in the baseline data having normal distribution and same variance. Wilcoxon rank sum test or Kruskal–Wallis *H* test will be used for the comparison of differences between groups that are not normally distributed or have uneven variance. Categorical variables will be tested by chi–square test or Fisher exact test. Wilcoxon rank sum test or Kruskal–Wallis *H* test will be used for the number of CSBM per week in primary outcome. Chi–square test or Fisher exact test will be used for percent improvement of each symptom scale score in secondary outcome indicators. The result of 48-h GITT will be analyzed using chi-square or Fisher test. Wilcoxon rank sum test or Kruskal–Wallis *H* test will be used for measurement data in HRAM, while chi-square test or Fisher exact test will be used for counting data. Safety, dietary quality, compliance indicators will be tested by chi-square test or Fisher exact test. Wilcoxon rank sum test or Kruskal–Wallis *H* test will be used to compare the diversity, the relative abundance of bacteria in phylum and genera level between 2 or more groups.^[22]^ Complying with the intent-to-treat (ITT) and per-protocol (PP) principle, all data of the patients randomized and at least 1 assessment (include baseline assessment) will be analyzed. For dropouts and terminations, their missing data will be obtained by last-observation-carried-forward (LOCF) method. All statistical analyses will be performed by SPSS20 software (IBM, Chicago, Illinois), and *P* value <.05 will be considered statistically significant.

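### The LOCF rule in section 2.15 does not exempt laboratory safety data, so an early stopper with no later blood sample is analysed on the pre-treatment value

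*Protocol article*

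**What the plan says.** Section 2.12.4 makes the laboratory tests part of the safety endpoint: "Safety parameters include AEs and laboratory examinations (BR, LKF".

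Section 2.8 gives their timing. After enrolment, patients complete "the relevant examinations (48-h GITT, HRAM, FFD, BR, LKF". The mid-treatment contact is remote: "On the 14th day, patients will be followed up via telephone to find out the situation during the treatment". Bowel movements, symptom scores and syndrome scores are named for that call; a blood sample is not. The next tests come after the full course ("The treatment period will last for 28 days"), when patients are seen again and staff are "to ask the patients to finish the examinations (48-hour GITT, HRAM, BR, LKF".

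Section 2.15 sets the analysis. A randomised patient with any one assessment is included, and the baseline assessment counts as one. The missing-data rule is general: "For dropouts and terminations, their missing data will be obtained by last-observation-carried-forward (LOCF) method". The test for safety is also given: "Safety, dietary quality, compliance indicators will be tested by chi-square test or Fisher exact test".

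Two other sections bear on harm. Section 2.10 applies "In case of any serious adverse events (SAEs) or emergency": a patient whose code is opened is treated as a dropout and leaves the efficacy analysis, but stays in the analysis of adverse reactions. Section 2.13 has adverse events reported throughout the study, with time, degree and duration entered in the case report form.

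**The concern.** LOCF needs a last observation. For BR and LKF the text provides one value before treatment and one at the end, with none between. If the second is missing, the first is carried forward, and a measurement made before any drug, placebo or diet becomes that patient's safety outcome.

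The effect on an arm's rate runs one way. A normal baseline carried forward can remove a treatment-related abnormality but cannot add one. The comparison between arms moves towards no harm whenever the arm with more abnormalities also loses at least as many of them, which is the expected pattern if harm leads to stopping.

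Safety of the diet is one of the things that the introduction and discussion say this trial will establish, and the herb powder is under test in the same design. Silent changes in liver or kidney function are what the laboratory endpoint adds to adverse event reports. An imputation rule that records unmeasured patients as unchanged weakens that part of the evidence.

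**Working it through.** **Inputs from the article**

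- Arm size: 23, with four arms per subtype (section 2.6). Check: 4 × 23 = 92, the stated number per subtype.
- BR/LKF sampling times in the text: enrolment and after 28 days (section 2.8).
- Missing-data rule: LOCF, baseline-only patients included, safety not excepted (section 2.15).
- Test: chi-square or Fisher exact, significance at P < .05 (section 2.15). Sidedness is not stated; two-sided is used here.
- Dropout rate and laboratory abnormality rate: not given.

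**Step 1: what LOCF enters.** With samples only at days 0 and 28, and day 28 missing, the last observation is day 0. The recorded change is zero.

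**Step 2: effect on one arm.** Let *a* be the patients in an arm of 23 who truly become abnormal, and *e* those among them who stop early without a later sample. Assume normal baselines and results classed as normal or abnormal.

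- All measured: *a*/23
- LOCF: (*a* − *e*)/23
- Shortfall under LOCF: *e*/23, or 1/23 = 4.3 percentage points per lost case
- Observed values only, with *s* early stoppers in all: (*a* − *e*)/(23 − *s*)

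The observed-only rate equals the true rate when *e*/*s* = *a*/23, that is, when stoppers are abnormal as often as the arm as a whole. LOCF falls short whenever *e* > 0.

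**Step 3: illustration.** The counts are assumed, since the article gives none. The comparator is 0/23, and every early stopper is taken to be a true case (*s* = *e*), which is the worst case for the observed-only analysis. P values are from Fisher's exact test.

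| True cases *a* | Stop early *e* | All measured | LOCF | Observed only |
|---|---|---|---|---|
| 4 | 2 | 4/23 = 17.4%, p = 0.109 | 2/23 = 8.7%, p = 0.489 | 2/21 = 9.5%, p = 0.222 |
| 6 | 2 | 6/23 = 26.1%, p = 0.022 | 4/23 = 17.4%, p = 0.109 | 4/21 = 19.0%, p = 0.044 |
| 6 | 3 | 6/23 = 26.1%, p = 0.022 | 3/23 = 13.0%, p = 0.233 | 3/20 = 15.0%, p = 0.092 |
| 6 | 6 | 6/23 = 26.1%, p = 0.022 | 0/23 | 0/17 |
| 8 | 4 | 8/23 = 34.8%, p = 0.004 | 4/23 = 17.4%, p = 0.109 | 4/19 = 21.1%, p = 0.035 |

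Two things follow. LOCF gives the lower rate whenever some cases are still observed. Dropping the imputation does not by itself recover the lost cases; only a sample taken at or after stopping can do that.

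**The case against.** Four points can be made for the plan.

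*A reader might infer that an early stopper has no on-treatment result at all.* The article does not say so. Section 2.8 describes patients who complete the course. The exit criteria (Table 1) and the study schedule (Figures 1 and 2) are not available in the text reviewed, and a condensed article may leave an exit visit or unscheduled tests to the full protocol. If such a sample exists, LOCF would carry that value and not the baseline one. This objection stands: the absence of an exit sample is not established.

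*A reader might infer that toxicity is hidden.* The documents do not support that. Sections 2.10 and 2.13 keep unblinded serious cases in the adverse reaction analysis and collect adverse events throughout. A patient who stops on day 10 with visible illness is counted as an adverse event whatever happens to the laboratory value. This stands too and confines the point to the laboratory endpoint, above all to silent change. It can also be said that a silent change is not in itself a reason to stop, which weakens the link between stopping and abnormal results.

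*The LOCF sentence is general and may be meant for efficacy.* An analysis plan could restrict it. But the sentence closes a section that has just set out the safety tests, contains no exception, and follows a statement that baseline-only patients are analysed. As written, it covers BR and LKF. This is a stated rule to correct, not a detail left out.

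*One post-treatment panel is a reasonable choice for a 28-day exploratory trial.* Agreed. The schedule is not the error; the imputation applied to it is.

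**Conclusion.** The point holds in a limited form. Section 2.15, applied as written to the sampling times in section 2.8, enters a pre-treatment BR or LKF value as the safety outcome of any early stopper who has no later sample. The patient stays in the denominator as unchanged, and the laboratory comparison is biased towards no harm.

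The unit of bias is 4.3 percentage points of an arm's rate per lost abnormality. This assumes a normal baseline, a patient who was abnormal by the time of stopping, and no unscheduled test. The number of such patients is unknown, so no total can be given; the table in the working is an illustration and not an estimate.

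The conclusion concerns only the laboratory endpoint. It does not show that patients go untested at exit or that clinically evident harm escapes the analysis. The change is still worth making, because the rule is explicit and correcting it costs almost nothing.

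**What to change.** **Section 2.15 (main change).** State that LOCF applies to efficacy outcomes only. Analyse BR and LKF in patients with at least one post-baseline sample. Count patients with none as missing, and report their number by arm and reason for stopping.

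**Section 2.8 and the exit procedure (secondary).** State whether BR and LKF are taken when a patient stops early or is unblinded. If the full schedule does not already provide this, collect the planned end-of-treatment sample at exit.

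**Cost.** The analysis change is a few sentences. The exit sample adds no test per patient, because it brings forward one already planned; the price is losing the day-28 value in a stopper who could still have attended then. Laboratory denominators become slightly smaller, some leavers will not come for the sample, and for them the observed-only rate can still understate harm. That is why the missing counts need to be shown by arm and reason.
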